### Intervention

#### Description of the intervention

In the IG, telemonitoring will consist of daily transfers of the following self-measured clinical parameters: respiratory-rate, heart-rate, blood pressure, blood oxygen saturation using pulse oxymetry, weight and body temperature. Together with the clinical data, patients will also complete a brief questionnaire aimed at assessing the patient's perception of his/her medical and functional condition. The questionnaire also contains items concerning compliance with medication and diet. Health professionals will check the data daily and will routinely contact the patient by phone every two weeks (nursing staff). Other telephone contacts will be carried out, if necessary, if the data received at the primary health care centre are out of the established limits. The telemonitoring system comprises personalised alerts set for each patient, with messages being sent to a Web-based platform when the recorded parameters fall outside established limits (which may be adjusted over time).

We have established standard initial threshold values for all the telemonitored parameters, which can be further modified by health care professionals according to the specific characteristics of the patients. The established threshold values are essential for the monitoring of the patient's condition and for the detection of unusual changes. When the measurements fall outside the established limits, alerts will be triggered via the PDA terminal and the clinical staff will act according to the medical condition of the patient. Alternatively, the patients will be advised to call the emergency services at the weekends and at times when the health centres are closed.

The standard threshold values for alerts are shown in Table 1.

**Table 1 T1:** Established thresholds for the telemonitored parameters.

Telemonitored parameters	Established threshold values
Respiratory-rate	< 12 or >24 breaths per minute (bpm)
Heart-rate	< 50 or >100 beats per minute (bpm)
Systolic blood pressure	< 100 or >160 millimeters of mercury (mmHg)
Diastolic blood pressure,	< 60 or >95 millimeters of mercury (mmHg)
Oxygen saturation	< 95% (this is a frequently adjusted limit for patients with CLD)
Temperature	> 37°C
Weight	Should be notified if there is an increase of 1 Kg in three days

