Qualitative questionnaire	Negative answers to the questionnaire which correspond to: feeling worse, breathing difficulties, increased nocturia, oedema, worsening of cough, increased sputum production and a change in sputum colour

In the CG, patients will receive usual care, consisting of regular medical examinations in line with the established programmes for monitoring home-based patients. The frequency of the medical examinations will vary depending on the clinical, social and family situation of each patient. Additionally, the GP and/or nurse will see or call the patient on demand in the event of a deterioration in the medical condition. Note that the IG will receive usual care, as well as the extra telemonitoring specified under the study protocol.

Prior to the intervention, all GPs and nurses in charge of the care of the participating patients (in both IG and CG) will attend a 4-hour workshop on the management of HF and COPD and early detection of relapses. Additionally, the health care professionals involved with the IG will receive further training on the use of the telemonitoring system. The key activities for the CG and IG are outlined in Figure 2.

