#### Technical features of the system and devices for data transfer and reception

The telemonitoring equipment, supplied by Saludnova [20], consists of a touch screen PDA which runs the Microsoft's Windows Mobile operating system, with wireless Bluetooth sensors to measure blood pressure, heart-rate and oxygen saturation, and manual input of body temperature, respiratory-rate, weight, questionnaires on the medical condition, any perceived changes and a record of compliance with medication and diet. The telemonitoring kit used by patients in the intervention group is shown in Figure 3. The data will be transferred via GPRS to the Web-based platform (Web data manager). The centralised Web management system allows different levels of access depending on the specific roles of the participating professionals (project leaders, GPs/nurses, hospital). The screen of the Web-platform accessed by health care professionals to check the transmitted data is shown in Figure 4. Although the platform can be accessed from any computer connected to the internet, it should be noted that there are terminals available in the consultation rooms of the health centres and in one of the referral hospitals (Santa Marina Hospital), which given its characteristics, often provides care to this type of patients.

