##### Cost assessment

Only direct unit costs per patient will be calculated. Indirect (caregivers, etc.) and intangible costs will not be considered for the analysis. The specific costs that will be taken into account include: costs directly associated with the telemonitoring intervention (cost of purchase and maintenance of the system, training of professionals in the use of the system, salaries of the health care professionals), costs associated with the home care (visits and telephone calls), costs related to the impact of the telemonitoring program on the necessary resources for the provision of patient care (number of visits to a primary care doctor, visit to the emergency department, number of hospital admissions). The costs will be based on 2009 figures and will be expressed in euros.

Health resources use estimates will be measured considering the following variables: number of telephone consultations (both control calls and calls made as a result of alerts) made or received by health care professionals (by the GP or nurse), average duration of telephone consultations, number of home care visits (both control visits and visits due to alerts) performed by health care professionals (by the general practitioner or nurse), average time spent by health care professionals to check the telemonitoring data daily, number of primary care visit, number of emergency department visits, number of visits to the specialist doctors and number of hospital admissions. The time taken to check telemonitoring data daily or undertaken monitoring telephone calls will be estimated by timing a sample of these tasks.

Resource use estimates will be combined with unit costs per patient obtained as follows: the time spent by health care professionals in made and answered telephone consultations and in checking the telemonitoring data daily, will be assessed based on the salaries for nurses and GPs as reflected in the Basque Health Service wage payment tables; primary care visits, emergency department visits and visits to the specialist doctors, will be amounted in accordance with the Osakidetza billing rates for health care services; hospital admissions will be assessed according to Diagnostic Related Groups (DRGs) for each pathologic condition; telemonitoring equipment (software and devices) will be assessed based on their equivalent annual cost, maintenance and training for their management will be valued using the market price provided by the supplier.

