The cost of telecommunications and computer equipment will not be considered, since this is an already implemented infrastructure in the Basque Health System, which is used for many other applications and daily tasks in addition to the telemonitoring process. The cost per patient will be minimal and, therefore, ignored in the costs calculation.

As the comparison is restricted to the programs under study, costs common to both need not be considered as they will not affect the choice between the given programs.

The costs will be based on 2009 figures and will be expressed in euros. The discount-rate used to calculate the equivalent annual cost will be 3%.

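### The reason given for leaving out telecommunications cost does not fit the GPRS link used only in the intervention arm; any omission would favour telemonitoring, by an amount the article does not allow one to determine

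*Protocol article*

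**What the plan says.** All statements are in the protocol article.

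- **Exclusion, first reason** (Cost assessment): "The cost of telecommunications and computer equipment will not be considered, since this is an already implemented infrastructure in the Basque Health System". The sentence goes on to say that this infrastructure also serves many other purposes.
- **Exclusion, second reason** (same paragraph): "The cost per patient will be minimal and, therefore, ignored in the costs calculation". No amount is given.
- **Common costs** (Cost assessment): "costs common to both need not be considered as they will not affect the choice between the given programs".
- **Intervention costs that are counted** (Cost assessment): "cost of purchase and maintenance of the system, training of professionals in the use of the system, salaries of the health care professionals". Software and devices enter at equivalent annual cost, and maintenance at the supplier's market price. Data transmission is not named as included in either.
- **Transfer route** (Technical features of the system): "The data will be transferred via GPRS to the Web-based platform (Web data manager". The same section says "The telemonitoring kit used by patients in the intervention group is shown in Figure 3", and describes the health-centre terminals separately.
- **Use by arm** (Description of the intervention): "In the IG, telemonitoring will consist of daily transfers of the following self-measured clinical parameters". For controls: "In the CG, patients will receive usual care, consisting of regular medical examinations".
- **Frame of the analysis** (Economic analysis; Presentation of the economic analysis): provider perspective, one-year horizon, a threshold of 30,000 euro per QALY, and bootstrapping as the sensitivity analysis.

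**The concern.** The exclusion is argued from sharing: the infrastructure is there anyway, other tasks use it, so little of its cost falls on any one patient. That argument suits consultation-room computers and the health service's own network. A mobile data connection from a patient's home is different. As described, it serves telemonitoring, and it has no counterpart in the control arm. The ground that a cost is common to both arms therefore does not cover it, and the claim that it is minimal cannot be inferred from sharing.

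What is at stake is a one-sided cost comparison. A charge borne by the provider in the intervention arm alone belongs in the incremental cost. The bootstrap would not reveal its absence, because resampling patients reproduces sampling variation in the costs that were recorded and says nothing about a cost that was never entered.

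**Working it through.** **Step 1: does each reason cover each item?**

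| Item | Existing and shared? | Common to both arms? | Amount given for minimal? |
|---|---|---|---|
| Health-centre computers and network | Yes, as described | Not needed; excluded as shared | No, but sharing makes it plausible |
| GPRS link from the patient's PDA | Not described as such | No, intervention arm only | No |

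**Step 2: direction.** Let c be the omitted provider cost per intervention patient-year, ΔC the true incremental cost, ΔQ the QALY difference and λ the threshold.

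- Net monetary benefit with the cost included: λΔQ − ΔC.
- With the cost left out: λΔQ − (ΔC − c) = λΔQ − ΔC + c.

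The benefit of telemonitoring is overstated by exactly c, whatever the threshold and in every quadrant of the cost-effectiveness plane. Where ΔQ is positive, the ICER is understated by c/ΔQ.

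**Step 3: size.** The article gives no tariff, QALY gain, incremental cost or ICER, so there is no stated figure to reproduce. The monthly charge and the QALY gain below are assumptions. Only the 30,000 euro threshold is from the article.

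Formulas: c = 12 × monthly charge; QALY equivalent = c/30,000; ICER shift = c/ΔQ.

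| Assumed charge (euro/month) | c (euro/year) | QALY equivalent | Shift at ΔQ = 0.01 | 0.02 | 0.05 | 0.10 |
|---|---|---|---|---|---|---|
| 2 | 24 | 0.0008 | 2,400 | 1,200 | 480 | 240 |
| 5 | 60 | 0.002 | 6,000 | 3,000 | 1,200 | 600 |
| 10 | 120 | 0.004 | 12,000 | 6,000 | 2,400 | 1,200 |
| 20 | 240 | 0.008 | 24,000 | 12,000 | 4,800 | 2,400 |
| 30 | 360 | 0.012 | 36,000 | 18,000 | 7,200 | 3,600 |

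The shift runs from 240 to 36,000 euro per QALY, that is from 0.8% to 120% of the threshold. The large entries arise from dividing by a very small assumed gain. The net-benefit scale is steadier: the provider loses c per patient, 24 to 360 euro over this range, or 720 to 10,800 euro for the 30 intervention patients.

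**The case against.** Four arguments can be made for the article as it stands.

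1. **The charge may already be counted.** Maintenance is valued at the supplier's price, which is not itemised and could include data transmission. The article also does not say who pays. If patients do, the charge lies outside the provider perspective. Both points stand, and they make the conclusion conditional. Against them, the equipment is described as software and devices, and telecommunications is excluded by name, so exclusion is the more natural reading. If the supplier's price does cover data, a sentence saying so is needed.

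2. **The exclusion may mean only the health service's own network.** It appears beside computer equipment and is described as shared. This reading is possible. The wording does not limit the exclusion in that way, and a person doing the costing could follow it either way.

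3. **The article breaks no rule of its own.** A reader might infer that only costs common to both arms may be left out, so that dropping an intervention-only cost contradicts the plan. The text does not support that. It permits common costs to be omitted; it does not forbid other omissions, and the paragraph before it makes a separate one. This objection stands in full.

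4. **The amount is probably small beside admission costs.** With the Sample size section's SD of 1.7 and 27 patients per arm (30 less 10%), the standard error of the difference in mean admissions is 1.7 × √(2/27) = 0.46. At an assumed 2,000 to 4,000 euro per admission, that is about 925 to 1,850 euro per patient, so 60 to 240 euro is about 3% to 26% of one standard error. The assumed reduction is 0.35 × 3.5 = 1.225 admissions, so an admission price of 240/1.225 = 196 euro would offset a charge of 240 euro. If telemonitoring both saves money and adds QALYs, an ICER shift means little. This supports ranking the point as minor. It does not remove it, because a systematic omission is not excused by being smaller than the sampling error.

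**Conclusion.** The concern holds in a limited form. The infrastructure reason does not fit the GPRS link of the intervention arm, and nothing in the article quantifies the claim that its cost is minimal. On two conditions that the article leaves open (the provider pays, and the supplier's price excludes data), following the stated exclusion understates incremental cost, and the error can only favour telemonitoring.

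The size is not determinable. Under an assumed 60 to 240 euro per patient-year, the omission is equivalent to 0.002 to 0.008 QALY per patient at 30,000 euro per QALY. This could be negligible or, with a very small QALY gain, noticeable.

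A reader might go further and infer that the ICER is certainly biased, or that it will be moved materially against the threshold. The article does not establish the first, because payer and price content are unstated. It cannot establish the second, because every figure except the threshold is assumed. Cost-effectiveness is a secondary outcome, and the comparison of hospital admissions is untouched.

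**What to change.** In the Cost assessment section:

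- Limit the exclusion to the computers and network that the health centres already had.
- State who pays for the GPRS data and whether the supplier's price includes it.
- If the provider pays and the price does not include it, add the data charge per intervention patient-month to the intervention cost.
- If the tariff is uncertain, vary it over a stated range in a deterministic sensitivity analysis alongside the bootstrap.

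The cost is one more cost line and a query to the supplier; no new patient data are needed. If the charge proves to be uncounted, the ICER becomes slightly less favourable to telemonitoring. If it is already in the supplier's price, only the clarifying sentence is needed and the result does not change.

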##### Presentation of the economic analysis

Once the QALY scores and the costs associated with the two care options under study have been estimated, the incremental cost-effectiveness ratio (ICER) will be calculated to determine which approach is most effective in terms of QALYs. To determine the degree of uncertainty, a sensitivity analysis will be carried out using the non-parametric bootstrapping method [36].

The ICER values estimated using bootstrapping re-sampling, together with the resulting distribution, will be used to estimate the 95% confidence intervals and will be plotted on a cost-effectiveness plane, to determine the quadrant in which the procedure under study lies (dominated, dominant, more costly and more effective or less costly and less effective). The cost-effective ICER proportions that lie, under the threshold widely accepted in Spain (30,000€/QALY) will be plotted using acceptance curves.

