### Sample size

Thirty patients will be recruited in each of the study groups, the main constraints being the number of available devices and the number of potential patients fulfilling the inclusion criteria in the Bilbao Primary Care Health Region. Thus, if 30 patients are included in each group, and a 10% loss to follow-up is assumed at 12 months (based on previous analysis of mortality and other causes of loss in patients with similar characteristics), we have estimated a statistical power of 72% to detect significant differences between the CG and the IG in the mean number of total admissions with a level of significance of 5%. For the power calculation, it has been assumed that the mean number of admissions in the CG is 3.5, the standard deviation 1.7, and there will be a 35% decrease of hospitalisations in the IG with respect to the CG [32-34]. The power calculations have been performed with the sample size calculation software Ene 2.0.

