#### Economic analysis of the telemonitoring intervention

A cost-effectiveness analysis will be undertaken from the perspective of the health care provider. The time horizon will be of one year.

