##### Assessment of the effectiveness

The QALYs, calculated from the EQ-5D questionnaire results, will be used as a measure of effectiveness. The QALYs will be estimated by calculating the area under the curve (AUC), which is obtained by summing up the areas of the geometrical shapes obtained by linear interpolation between the utility scores during the study period [35]. In addition, the baseline utility will be controlled using a regression-based adjustment, since there tends to be a strong correlation between the baseline utility of patients and the QALY scores [35].

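### A 95% confidence interval taken from bootstrap ICER values can be uninterpretable when resamples cross a zero QALY difference, and the acceptability-curve rule needs clarifying

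*Protocol article*

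**What the plan says.** The relevant text is in the protocol article under Presentation of the economic analysis. It makes four statements.

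- Purpose of the ratio: the ICER "will be calculated to determine which approach is most effective in terms of QALYs".
- Uncertainty: "a sensitivity analysis will be carried out using the non-parametric bootstrapping method".
- Interval: "The ICER values estimated using bootstrapping re-sampling, together with the resulting distribution, will be used to estimate the 95% confidence intervals". The same sentence plots the resamples on the cost-effectiveness plane, with this aim: "to determine the quadrant in which the procedure under study lies (dominated, dominant, more costly and more effective or less costly and less effective").
- Acceptability curve: "The cost-effective ICER proportions that lie, under the threshold widely accepted in Spain (30,000€/QALY) will be plotted using acceptance curves".

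The effect measure is the QALY (Assessment of the effectiveness: "The QALYs, calculated from the EQ-5D questionnaire results, will be used as a measure of effectiveness"), over a short horizon ("The time horizon will be of one year"). The trial is small (Sample size: "Thirty patients will be recruited in each of the study groups", with 10% loss assumed at 12 months).

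The text names no interval type, no net-benefit calculation and no rule for resamples in which telemonitoring yields fewer QALYs than usual care.

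**The concern.** The ICER is the cost difference divided by the QALY difference. Its meaning depends on the quadrant, and it jumps from one extreme to the other as the denominator passes through zero. An interval formed by ordering bootstrap ratios makes sense only if practically all resamples lie on one side of that point. The plan itself allows for all four quadrants, yet takes the interval from the distribution of the ratio without qualification.

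Two related statements add to the problem. The ratio is given the task of showing which approach yields more QALYs, which it cannot do. The curve is described through ratios under a threshold, which is safe only if this means points below the threshold line on the plane.

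At stake is the reported uncertainty of the cost-effectiveness result, a named secondary objective. The primary analysis of admissions is not affected.

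**Working it through.** The economic section states a threshold but no computed result, so there is no figure of the plan to reproduce. The 72% power under Sample size concerns admissions and has no bearing here.

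**1. Why the ratios cannot be ordered.** Write dE for the QALY difference and dC for the cost difference (telemonitoring minus usual care). Then ICER = dC/dE, and net monetary benefit NMB = 30,000 × dE − dC. Five illustrative resamples:

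| dE | dC (euro) | ICER | Ratio under 30,000? | NMB (euro) |
|---|---|---|---|---|
| +0.05 | −1,000 | −20,000 | yes | 1,500 + 1,000 = +2,500 |
| −0.05 | +1,000 | −20,000 | yes | −1,500 − 1,000 = −2,500 |
| +0.05 | +1,000 | +20,000 | yes | 1,500 − 1,000 = +500 |
| −0.05 | −1,000 | +20,000 | yes | −1,500 + 1,000 = −500 |
| −0.05 | −2,000 | +40,000 | no | −1,500 + 2,000 = +500 |

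Rows 1 and 2 share a ratio, but one is dominant and the other dominated. Rows 3 and 4 share a ratio and lead to opposite decisions. Sorting on the ratio therefore mixes good and bad results at both ends. The jump at zero is as troublesome: with dC = +1,000, moving dE from +0.001 to −0.001 takes the ICER from +1,000,000 to −1,000,000, while NMB only moves from 30 − 1,000 = −970 to −30 − 1,000 = −1,030.

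**2. How likely resamples are to cross zero.** Patients per arm: 30, or 30 × 0.90 = 27 after the assumed loss. The documents give no SD for QALYs or costs, so a range is assumed. With a true gain of 0.05 QALY, the share of resamples with dE < 0 is Φ(−0.05/SE):

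- SE 0.03: Φ(−1.67), about 5%
- SE 0.068 (SD 0.25 at 27 per arm: 0.25 × √(2/27)): Φ(−0.73), about 23%
- SE 0.075: Φ(−0.67), about 25%

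**3. What the ratio interval then looks like.** One million bivariate normal draws stand in for the bootstrap. Assumed: SD 0.25 QALY and 6,000 euro per patient, 27 per arm, no correlation, so the SEs are 0.068 QALY and 6,000 × √(2/27) = 1,633 euro. Percentile limits are used for illustration.

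- dE 0.05, dC 0: about −232,000 to +233,000 euro per QALY (23% of draws with dE < 0)
- dE 0.15, dC 0: about −39,000 to +39,000 (1.4% with dE < 0)

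For the first case NMB is well behaved. Mean = 30,000 × 0.05 − 0 = 1,500 euro. SE = √[(30,000 × 0.06804)² + 1,633²] = √(2,041² + 1,633²) ≈ 2,614. The 95% CI is 1,500 ± 1.96 × 2,614, about −3,620 to +6,620 euro.

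**4. The curve, if its rule were a bare ratio under 30,000.** Same assumptions as step 3:

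| dE | dC (euro) | Share with ICER < 30,000 | Share with NMB > 0 |
|---|---|---|---|
| 0 | 0 | 78.5% | 50.0% |
| 0 | +2,000 | 69.1% | 22.2% |
| 0.05 | +2,000 | 63.6% | 42.5% |
| 0.05 | 0 | 82.4% | 71.7% |
| 0.05 | −2,000 | 82.9% | 90.9% |
| 0.15 | 0 | 96.1% | 95.7% |

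For dE 0.05 and dC 0 the gap decomposes as 71.7 + 11.6 (dominated, counted) + 5.3 (less costly and less effective, wrongly counted) − 6.2 (less costly and less effective, wrongly rejected) = 82.4. With dC −2,000 the last term is 15.6 and the net error turns against telemonitoring: 90.9 + 2.6 + 5.0 − 15.6 = 82.9.

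Over SDs of 0.1 to 0.3 QALY and 3,000 to 10,000 euro, at dE 0.05 and dC 0, the bare ratio overstates the share by about 0.3 to 20 percentage points.

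**5. Purpose of the ICER.** Rows 1 and 2 of the first table have the same ICER, with telemonitoring ahead on QALYs in one and behind in the other. The ratio cannot say which arm is more effective; dE can.

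**The case against.** The best defence is that the section is loosely worded rather than wrong. A reader might infer that the plan counts dominated resamples as successes. It does not say so. It places resamples on the plane, distinguishes dominated from dominant, and speaks of cost-effective proportions, and a dominated resample is not cost-effective. Read together, this fits the usual count of points below the threshold line, which is the same as NMB > 0. A condensed article may also leave the counting algorithm to a fuller document. This defence stands for the curve, which is therefore an ambiguity to remove and not an established error.

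A reader might also infer that the results would mostly favour telemonitoring. The figures do not support that: even under the bare-ratio reading, the error works against telemonitoring when it saves money.

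Nor can it be said that the QALY difference will almost certainly straddle zero. No variability is given, and the planned adjustment for baseline utility (Assessment of the effectiveness) should reduce the standard error.

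The remark on the purpose of the ICER can be called a slip, since QALYs are estimated first and their difference will be available. That limits its consequences, but the statement is still incorrect.

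The defence does not reach the interval. The plan names no interval type, and percentile limits are used here only as an illustration, but it does say that the interval comes from the distribution of ICER values. Any interval that relies on ordering those values has the same fault. This is a stated method, not a detail left out.

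**Conclusion.** The point holds for the interval. As written, the 95% CI comes from the bootstrap distribution of a ratio that has no usable ordering once resamples cross a zero QALY difference, in a plan that itself allows for all four quadrants. With 27 to 30 patients per arm such crossing is plausible but not certain: about 5% to 25% of resamples at a true gain of 0.05 QALY and assumed SEs of 0.03 to 0.075. If practically all resamples show a QALY gain, the problem largely disappears.

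The stated purpose of the ICER is incorrect. The curve rule is ambiguous. Only under the literal reading would it be wrong, by a fraction of a point to some tens of points depending on the assumed effect and variability, and in either direction.

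All sizes rest on assumed QALY and cost variability and on normal draws in place of real resamples. The consequence is confined to the secondary economic analysis. The change is worth making because it replaces a stated method that can fail with one that does not, at no cost.

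**What to change.** Amend Presentation of the economic analysis, using the same bootstrap resamples:

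- Replace the confidence interval for the ICER with incremental net monetary benefit at 30,000 euro per QALY and its 95% CI. Report the separate cost and QALY differences, each with a 95% CI.
- Define the acceptability curve as the proportion of resamples in which threshold × QALY difference − cost difference exceeds zero, plotted over a range of thresholds that includes 30,000 euro.
- Report the ICER as a point estimate only, with its quadrant stated.
- Correct the stated purpose: the QALY difference shows which approach is more effective, and the ICER expresses the cost per QALY of the trade-off.

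The plot on the cost-effectiveness plane can stay as planned. No new data, resampling or design change is needed; only the summary of the existing output changes.
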